#### Group 2 standard of care (LVP)

Participants randomised to LVP [3], the current standard of care, will be admitted to hospital as either a self-referral or via their GP, whichever is current local practice. They will undergo LVP as clinically indicated. LVP involves the insertion of a peritoneal drain for up to 6 h and removal of up to 15 L of ascites. If the total volume of fluid to be removed is > 5 L, intravenous 4.5% or 20% (w/v) human albumin solution, 8–10 g per 1 L of ascitic fluid removed, will be administered [3].

As with Group 1, participants will receive antibiotic prophylaxis (ciprofloxacin 500 mg once a day or an equivalent antibiotic (if there is any contraindication to ciprofloxacin), dependent on local practice).

For both groups there will be two weekly visits with a research team member for questionnaire-based and clinical assessments as well as routine clinical blood samples (as discussed in subsequent sections). We anticipate that these two weekly contacts will improve adherence to the protocol.

### Clinical follow-up

While participating in this trial, for no individual will routine clinical care be modified or denied whether in the community, primary care or hospital setting. This will include symptomatic relief for pain (including use of opioids), shortness of breath, confusion (hepatic encephalopathy), jaundice or itching. Use of diuretics will be permitted in both groups. As is the current standard of care in patients with ESLD, the use of certain drugs (e.g. non-steroidal anti-inflammatory drugs, aminoglycosides) will be contraindicated [3].

Palliative care needs and concerns will be reassessed at each visit for each participant using the Integrated Palliative care Outcome Scale (IPOS) questionnaire [28] (see subsequent sections). If a high level of specialist palliative care need is identified (as defined within a distress protocol standard operating procedure [SOP]), through the IPOS questionnaire, a research team mini MDM (either face-to-face or virtual) will be convened to agree on the most appropriate way forward. As is standard clinical practice, referrals to a specialist service by the usual healthcare providers can also occur irrespective of any trial assessments or advice. If that occurs, consistent with standard practice, a referral is simultaneously made to a community (district) nurse, if this was not already done for another reason.

It may become necessary, after discussion with the CI and the Trial Management Group (TMG), to remove the LTAD. Reasons for this could include (1) patient request, (2) serious adverse reaction (SAR) assessed by the CI as being directly related to the LTAD and (3) significant deviation from the study protocol with potential for harm (for example the participant not allowing community nurses to enter residence to perform drainage).

The contact telephone numbers for key members of the research team will be provided to the participants. Out of hours, participants will be encouraged to contact their GP or attend the accident and emergency department of their local hospital, as per usual standard of care.

### Outcome measures

The objectives of this feasibility study therefore are to explore:Properties of different outcome measures (specifically health resource utilisation and QOL instruments) to ascertain the most appropriate primary outcome for the full trial and use the chosen primary outcome measure to inform sample size calculations from estimates of the standard deviations, for the full trialResource implications of the LTAD compared to standard of care (LVP), including a preliminary assessment of cost-effectiveness to indicate whether a full trial is worthwhileThe number of eligible patientsThe extent of HCP support in identifying possible participantsSymptom burden in patients with ESLD and refractory ascitesInformal carer/family perceived burden (if appropriate)Whether patients are willing to be randomised to LTAD, rather than LVPAcceptability of and adherence to home ascites drainageAttrition rates, including attrition due to death, illness or other causesComplication rates inclduing peritonitisWillingness to participate in a qualitative interview (optional)Acceptability of the LTAD to patients, carers and clinical staff using qualitative methods (optional)Acceptability of questionnaires

We will therefore collect data on a range of candidate primary outcome measures, including QOL and health resource utilisation. The primary outcome measure(s) for the definitive trial will be decided by the research team, including service users, on review of the final analysis of this feasibility study.

### Study success criteria

The study success will be based on the following criteria:The percentage of study period time in hospital for the LTAD group is < 50% of that for the LVP group (where the study period time is the number of days from the date of LTAD insertion to the end of the study period or the patient’s death (whichever is earliest); time spent in hospital is the number of bed days used).The attrition rate is not > 50%.There is < 10% overall rate of LTAD removal due to one or more of the following complications: peritonitis, failed insertion, bleeding and blockage.Each patient has completed 80% of the questionnaires and qualitative interviews.

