### Characteristics of participants

Patients will be identified from acute medical units, outpatients and gastroenterology and hepatology wards. They will be approached for the study at the participating centres by the research team after having been identified by the local medical team as being potentially eligible.

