### Randomisation

Patients who fulfil the inclusion and exclusion criteria and give written informed consent to participate in this trial will be randomised on a 1:1 basis to either Group 1: LTAD or Group 2: LVP (current standard of care). The allocations will be made by minimising on (1) centre, (2) Child-Pugh score and (3) gender. No stratification will be utilised. Minimisation will be implemented using an independent system hosted at King’s Clinical Trials Unit (KCTU). Patients will be enrolled by the research team member, who will log into the web-based system and enter patient ID number, recruiting site, gender and Child-Pugh score. The system will automatically generate a confirmation email informing the research team of the outcome of allocation.

Patients will be followed up for 12 weeks. With the participants’ agreement we will inform their GPs about their participation in the trial.

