### Data analysis

#### Statistical analysis

Guidelines for feasibility studies suggest that analysing 12 participants in each arm will provide an adequate sample size with which to achieve our objectives [42]. However, since this is a cohort with a poor prognosis, attrition is likely to be high. In our pilot study of seven patients [26], survival post insertion ranged from 6 to 96 days (though the LTADs were inserted late in the disease trajectory). Due to the advanced disease stage of the participants, we are assuming a 50% attrition. The sample size will therefore be increased to 24 participants in each arm, i.e. a total recruitment target of 48 participants. This sample size will be adequate to inform the research methods for a definitive phase 3 RCT.

Recruitment rate will be evaluated in terms of the proportion of eligible patients who provide informed consent. Attrition at all stages will be recorded, particularly due to unwillingness or inability to manage the LTAD, as this is an indication of acceptability. Data will be analysed on available cases in the groups to which they were randomised. We will present these data as a flow chart. The amount of missing data will be summarised for each variable, but there will be no imputation. As this is a feasibility study, stopping rules will not be defined.

The flow of patients through the trial is depicted in the Consolidated Standards of Reporting Trials (CONSORT) diagram (Fig. 4) [43].

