**Fig. 4 Fig4:**
[figure not shown]
Consort flow chart

Descriptive statistics will be used to summarise and compare the quantitative outcome measures to include (1) complication rates: failed insertion, drain leakage or blockage, cellulitis, bleeding, pain at site of insertion not controlled by analgesia, peritonitis, sepsis and death (the latter two only if directly related to the LTAD), (2) symptoms: IPOS, QOL (SF-LDQOL, EQ-5D-5 L) [28, 33–35] and (3) carer burden [36, 37] for each arm. Means and standard deviations will be determined for normally distributed outcomes and medians and interquartile ranges for skewed outcomes at the different time points and at the end of the study. Analyses will use all available cases following intention-to-treat principles. We will calculate 95% confidence intervals for parameter estimates as appropriate. Prior to the analysis of the data, a detailed statistical analysis plan will be written and signed off.

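### Success criterion 1 starts the hospital-time clock at LTAD insertion, so the ratio is undefined for the LVP arm and the two arms are not comparable

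*Protocol article*

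**What the plan says.** Under Study success criteria, the protocol article sets the first criterion as "The percentage of study period time in hospital for the LTAD group is < 50% of that for the LVP group". It then defines both parts of the percentage. The denominator is given by "where the study period time is the number of days from the date of LTAD insertion to the end of the study period", or to death if that comes first. The numerator is given by "time spent in hospital is the number of bed days used". No other start date is offered for either arm.

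Four other places bear on this:

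- Group 2 standard of care (LVP) says of the comparator patients: "They will undergo LVP as clinically indicated". No LTAD insertion is planned for them.
- Randomisation says "Patients will be followed up for 12 weeks". It does not say from which date.
- Procedure for insertion of LTAD treats insertion as a planned step, separate from randomisation, with clotting checked in the week before. It prefers a single insertion site and allows local insertion. It gives no interval from randomisation to insertion.
- Statistical analysis says "Data will be analysed on available cases in the groups to which they were randomised" and, after the CONSORT flow chart, "Analyses will use all available cases following intention-to-treat principles".

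**The concern.** A two-arm ratio needs a clock that exists in both arms and starts at the same point. This one starts at an event that only one arm can have.

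Three consequences follow from the text:

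1. The LVP percentage cannot be computed as defined, so neither can the ratio.
2. In the LTAD arm, days, bed days and deaths between randomisation and insertion fall outside the period. A patient randomised to LTAD who dies, declines or otherwise never reaches insertion has no period at all. For a failed insertion, which the third success criterion anticipates, the start date is unclear.
3. A start date that depends on receiving the device sits badly with analysis by randomised group on intention-to-treat principles.

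This is the only one of the four success criteria that compares the arms. The health economics section also lists the number of hospital days among the measures to be examined for the definitive trial's primary outcome. If the origin is left open, someone will have to choose it, possibly after the hospital data have been seen.

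**Working it through.** **The plan's own figure.** The only sample-size arithmetic reproduces: 12 / (1 − 0.5) = 24 per arm, and 2 × 24 = 48. It does not bear on this point. The article gives no projected value for criterion 1, so what follows is a reading of the definition and then an illustration.

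**Is the definition computable?**

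| Element | LTAD arm | LVP arm |
|---|---|---|
| Start of period | Insertion date | No such date |
| Time from randomisation to start | Left out | Cannot be said |
| Patient never reaching insertion | No period | Every patient is in this position |

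**Scale of hospital use.** The Background describes LVP every 10–14 days with a 24–48 h admission, taken here as 1–2 bed days. Over 12 weeks (84 days):

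- low: 84 × 1/14 = 6.0 bed days, or 7.1%
- middle: 84 × 1.5/12 = 10.5 bed days, or 12.5%
- high: 84 × 2/10 = 16.8 bed days, or 20%

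These count LVP admissions only. The criterion counts all bed days.

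**Does the origin matter?** Assumptions not in the article: LVP-arm rate L = 0.125; period ending 84 days after randomisation; LTAD arm with 1 bed day for insertion plus 4% of post-insertion days in hospital; a wait of w days with hospital rate h; no deaths.

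- Post-insertion bed days: B = 1 + 0.04 × (84 − w)
- Insertion clock: ratio = [B / (84 − w)] / L
- Randomisation clock: ratio = [(B + h·w) / 84] / L

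For w = 14, B = 1 + 0.04 × 70 = 3.8:

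- insertion clock: (3.8 / 70) / 0.125 = 0.434, pass
- randomisation clock, wait at the LVP rate: ((3.8 + 0.125 × 14) / 84) / 0.125 = (5.55 / 84) / 0.125 = 0.529, fail
- randomisation clock, no bed days in the wait: (3.8 / 84) / 0.125 = 0.362, pass by a wider margin

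| Wait (days) | Insertion clock | Randomisation, wait at LVP rate | Randomisation, no bed days in wait |
|---|---|---|---|
| 0 | 0.415 | 0.415 | 0.415 |
| 7 | 0.424 | 0.472 | 0.389 |
| 14 | 0.434 | 0.529 | 0.362 |

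**Where the sign turns.** The two clocks agree when the hospital rate in the wait equals the post-insertion rate, insertion stay included. For w = 14 that is 3.8 / 70 = 5.4%, or 0.054286 × 14 = 0.76 bed days in the wait. Above this the insertion clock favours LTAD; below it, the clock works against LTAD. The verdict changes once total LTAD bed days reach 0.5 × 0.125 × 84 = 5.25, that is, with 5.25 − 3.8 = 1.45 or more bed days in the wait.

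**The case against.** The strongest reply has three parts.

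First, this is a feasibility trial with no hypothesis test. The article condenses a fuller protocol, promises a detailed analysis plan before analysis, and refers to a timeline and schedule that are not shown here. Any of these might anchor the period in both arms. That lowers the stakes but does not remove the point. The article does not leave the definition open; it states one, and that one fails for the comparator.

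Second, the criterion excludes nobody in words, and the analysis section keeps patients in their randomised groups. This stands in part: the text is silent on patients without a drain and does not expressly drop them. But under the stated rule they have no denominator, so the two statements cannot both be applied.

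Third, a reader might infer that the insertion clock is biased toward LTAD, because it discards waiting time that patients largely spend in hospital, and that it could by itself deliver the required halving. The article does not support that. It gives neither the length of the wait nor the bed days in it. On recruitment it says "Patients will be identified from acute medical units, outpatients and gastroenterology and hepatology wards", which includes outpatients and gives no proportions. Planned insertion is compatible with waiting at home. The insertion stay itself is already counted, over a shortened denominator. And no sign exists until an LVP start date is chosen. A favourable direction is plausible, since patients waiting for a drain may still be admitted for LVP, but it is conditional. This objection to a stated direction stands in full.

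**Conclusion.** The point holds as a fault in a stated rule. As written, the criterion has no comparator percentage. It leaves out the LTAD arm's time from randomisation to insertion and gives no period to patients who never reach insertion, which does not fit the stated intention-to-treat approach. The undefined comparator and the omitted interval follow from the text alone and need no assumption.

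The size and sign do need assumptions. In the illustration, moving the origin from insertion to randomisation takes the ratio from 0.434 either up to 0.529, across the 0.50 threshold, or down to 0.362, depending only on hospital use during an assumed 14-day wait. With no wait the two clocks agree. So the choice of origin can decide the criterion, but the article does not show which arm gains. The figures rest on the assumed wait, the 12.5% LVP rate taken from the middle of the article's own ranges, the assumed LTAD rates, and a period ending 84 days after randomisation with no deaths. They show sensitivity and are not forecasts.

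**What to change.** Reword the first success criterion so that, in both arms:

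- the study period runs from the date of randomisation to the end of the 12-week study period or death, whichever is earlier;
- all bed days in that window count, including the insertion admission;
- every randomised patient is included in the allocated arm, whether or not a drain was placed.

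Fix this before hospital use is compared between arms. Pooling total bed days over total patient-days alive in each arm, and giving a confidence interval for the ratio, would be sensible additions, but neither is needed to cure the fault.

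The cost is wording. Service use assessment already has all hospital use taken from hospital records at the end of the study, and the randomisation system should hold the start date. The LTAD figure may move in either direction, and the team should accept that before seeing it. If time from insertion is of interest, describe it separately for the LTAD arm and do not use it for the ratio.

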### Data collection

Data will be collected on an electronic case report form (eCRF), using the MACRO electronic data capture system provided by KCTU and hosted on the King’s College London (KCL) server. The system is compliant with Good Clinical Practice (GCP), with a full audit trail and formal database lock functionality.

Figure 2 shows the participant timeline/study flow chart.

**Fig. 2 Fig2:**
[figure not shown]
Participant timeline

### Schedule of assessments

The research team member will visit participants at home every 2 weeks for questionnaire-based and clinical assessments (see the subsequent section) as well as collection of routine clinical blood samples. The amount and frequency of drainage and other pertinent observations will be recorded by community nurses in a formal study diary, as is the case when the LTAD is used in patients with ascites due to malignancy. The research team member will train and advise the community nurses and participants on data collection to reduce the possibility of missing data. See Fig. 2 and the Standard Protocol Items: Recommendations for Interventional Trials (SPIRIT) schedule (Fig. 3).

**Fig. 3 Fig3:**
[figure not shown]
SPIRIT schedule

### Questionnaire-based assessments

The questionnaire-based assessments will be performed by the research team member and, depending on patient preference, will be done either face to face at the patient’s home or via telephone (within 3 days of the research team member visit). The research team member will follow guidance in the lone worker policy when conducting home/usual place of care visits.

We have selected questionnaires validated with our population group (e.g. palliative care patients and those with ESLD). Some, like the IPOS [28] (see the following section), are short, relatively brief to complete and have a proxy version if a patient loses capacity during the study. As this is a feasibility study, we will explore the acceptability of the measures used. We will pilot the patient questionnaires comprising the proposed measures with the first eight patients to explore and assess patient fatigue and time taken for completion. We will review the pilot findings and amend the patient questionnaire schedule if indicated, submitting the required Research Ethics Committee (REC) amendment for all proposed changes. The research team member will assist the participants in completion of the questionnaires if needed and if specifically requested by the participant. If participants are too unwell, the questionnaires can be completed by proxy by the carers, to reduce both the participant burden as well as the risk of missing data. Additionally, for those patients allocated to the LVP group, if the hospital visits coincide with questionnaire assessments, the assessments can be done at that point in hospital.

### Symptom distress and concerns

The IPOS [28–30] combines the Palliative care Outcome Scale (POS) and POS-S (POS with symptom list). These are measures frequently used in palliative care research and clinical practice [28–32]. They are validated for clinical practice, audit and research and can be used in any setting. The POS-S captures physical symptom specific information, and “other” symptoms specific to liver disease/ascites can be added, e.g. abdominal bloating. A SOP will be implemented when clinical and/or risk of harm issues are identified to ensure timely assessment by their usual healthcare providers and/or referral to a specialist palliative service depending on needs identified.

A staff version of the IPOS will be used in case participants are unable to complete the questionnaire. The IPOS will be assessed at baseline and two weekly and takes less than 10 min to complete (a total of 10 questions).

### Quality of life

QOL will be assessed using the Short Form Liver Disease Quality of Life (SF-LDQOL) [33, 34], a reliable and valid measure of health-related QOL in patients with advanced liver disease awaiting transplant, incorporating a core QOL assessment and disease targeted items. As specific QOL assessment tools are lacking in cirrhosis, the SF-LDQOL is the most appropriate option and was selected after service user involvement. The original SF-LDQOL questionnaire has 43 questions, though the questions from 26 onwards are for the purposes of validating the questionnaire and not specific to the SF-LDQOL itself [33, 34]. The authors have provided a scoring algorithm that includes only the first 25 questions; therefore, only these questions will be used. This questionnaire takes about 15 min to complete and will be assessed at baseline and four weekly.

### Health economics outcome

There are opposing views on the use of the EuroQol 5 dimensions (EQ-5D) as a composite measure of quality-adjusted life years (QALYs) in palliative care [18]. However, it is the most widely used indicator, and until valid alternatives are available, we have elected to assess the 5-level version (EQ-5D-5 L) [35] (at baseline and four weekly) in this feasibility study for its utility as an outcome. The EQ-5D-5 L has six questions and will take about 5 min to complete.

### Impact on carers

For those willing to participate, the Zarit Burden Interview (ZBI-12) [36, 37] will be employed at baseline and four weekly. The ZBI-12 measures family/informal carer appraisal of the impact of caregiving. It has 12 items, is easy to administer and it can be used in the hospital or community setting, taking about 10 min to complete.

### Service use assessment

For each arm of the feasibility study, a comprehensive patient-level database of services used will be collated, including all inpatient, outpatient, emergency, primary, community, social and voluntary services, equipment and supplies and assistance from family/informal carers. For community and home-based services, a modified version of the Ambulatory and Home Care Record (AHCR) [38] will be used and administered by the research team member at baseline and two weekly. The carers will assist with this, especially if the participant is too unwell. The AHCR, a standardised and comprehensive framework and tool, measures resources used within the end-of-life context from a societal perspective. This approach gives equal consideration to costs borne by the health system as well as those costs borne by care recipients and informal caregivers, such as family members and friends. It will take about 20 min to complete. Self-reported data will be verified and supplemented (e.g. for supplies) with reference to nursing records. Data on all hospital use will be gathered from hospital records at the end of the study using a purposefully designed in-house proforma. Service use will be converted to costs using national sources [39] and National Health Service (NHS) reference costs. Informal care will be valued using replacement cost methods and applying the tariff for community support workers.

A feasibility study gives us the opportunity to test candidate patient-reported outcome measures with the intention of only taking the most useful measures through to any definitive study. Survey fatigue was always a concern for the research team and our service users, and the issue also arose during the Ethics Committee review process. Therefore, we had a safety check to reassess survey fatigue after the first eight patients were recruited. We have found no evidence of any problems so far; indeed some patients restate their willingness to complete the questionnaires.

